# The Neu-Prem Trial: Neuromonitoring of Preterm Newborn Brain During Birth Resuscitation

**Principal Investigator**: [name]

**Co-Investigators:** [name],

**Consultant:** [name]

**Length of Study**: 2 years

# Number of subjects to be studied: 130

**Age range of subjects**: Premature newborns between 23 to 32 weeks gestation

PROPOSAL NARRATIVE.

**Goals, hypothesis and objectives.** The goal for this trial is to characterize the normal brain function of 130 very premature newborns (23 to 32 weeks gestation) during the first 72 hours of life. This is the first observational study to evaluate brain perfusion and function in 130 premature newborns ***starting at the time of birth.***

Our primary hypothesis is that simultaneously recording physiological changes of the newborn (brain activity, brain oxygenation, blood pressure, blood oxygenation, cardiac function and heart rate) beginning at birth will help us predict which babies will develop adverse problems such as bleeding in the brain (intraventricular hemorrhage, IVH) and its resultant neurological problems. We hypothesize that newborns **with low brain perfusion** and **low brain activity** at birth will have **poor outcomes** such as bleeding in the brain and death. We will measure these components of brain function using two sophisticated, non-invasive technologies. First, amplitude integrated electroencephalography (aEEG), a “simplified” EEG with four sensors (single channel), enables continuous non-invasive monitoring of cerebral activity. Second, near-infrared spectroscopy (NIRS) provided by FORE-SIGHT Elite Absolute Tissue Oximeter, is another non-invasive technology that allows continuous real-time measurement of regional tissue oxygen utilization of the brain. Both technologies are FDA approved in newborns and have been predictive of brain injury or neurodevelopmental impairment. [1-9]

Our proposal builds on an ongoing research program at a nationally recognized level 3 center with the largest number of births in California. With several completed and ongoing trials in preterm infants, our group is uniquely positioned to lead this clinical trial. (ClinicalTrials.gov:

NCT01866982, NCT02231411, NCT02195037, [10, 11]) For example, we demonstrated a heart rate can be detected using ECG leads in the delivery room much quicker compared to an oxygen saturation monitor (pulse oximeter). [12] We have also demonstrated interventions at birth (such as squeezing or milking the umbilical cord before it is cut) that provide better blood flow in babies at 6-30 hours of life. [10] It is reasonable to infer, though it is not yet proven, that these newborns *with better blood flow* had improved brain activity and improved perfusion.

**No previous study has linked measures of brain activity and oxygenation beginning at birth to neonatal outcomes.** Newborns who require extensive resuscitation (e.g. CPR or breathing assistance) are at greater risk for hypoxic-ischemic encephalopathy (HIE) and brain injury. [13, 14] Preterm infants that require more resuscitation have a higher rate of brain bleeding and death. [15]

Heart rate by ECG (electrocardiogram) is now being recommended for use in premature newborns as a method to determine heart rate compared with conventional methods of auscultation and pulse oximetry. However it is unclear as to whether the availability of a heart rate by ECG would impact the amount of resuscitation needed by premature newborns. Therefore we will make ECG available in half of the infants (by randomization at the time of delivery by the research team, in opaque sealed envelopes) and record the amount of resuscitation needed. This will allow us to implement a recommended intervention to become our standard practice. Furthermore, since heart rate is an existing outcome in the delivery room it will not change the amount of data required for parental consent.

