# Size of the population to be studied in terms of age, gender, ethnicity, the source of subjects and the recruitment process.

In 2014 more than 9,400 babies were born at Sharp Mary Birch Hospital for Women and Newborns, and 1,500 babies were admitted into the NICU. In our most recently completed trial in premature infants with identical eligibility criteria (23-32 weeks gestation), we recruited 150 subjects in less than 2 years. (Platform Presentation: Katheria et al, E-PAS 2015). Therefore, we are confident that we will be able to enroll the 130 newborns needed over the two year grant period. This figure is also conservative to include a parental refusal rate of 20 percent since we do not anticipate many parents would refuse to participate given the minimal risks of the study. Every premature newborn from 23 to 32 weeks gestation born at Sharp Mary Birch will be considered for enrollment until we reach our target of 130 newborns over the two year period.

**Study Timeline:** We anticipate it will take 18 months to recruit 130 infants and six months to

collect and analyze data for publication and presentation at a national meeting (total 24 months). We do not anticipate that any subjects would drop out since the intervention is performed at birth.

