# RECRUITMENT AND RETENTION OF SUBJECTS

***Recruitment/Consent/Stratification:*** Sharp Mary Birch Hospital for Women & Newborns and the Neonatal Research Institute (NRI) has an in-house parent advisory group that reviews trial designs to determine how parents may feel about them and whether the consent is clear and appropriate. A waiver for delayed consent is proposed in order to successfully complete the trial with minimal selection bias in a reasonable period of time. The research presents no more than minimal risk of harm to subjects. There are no known long term consequences of having leads applied to the surface of the skin. We now have compelling evidence that trials which require consent before delivery are likely to enroll a population that is not as sick as those eligible but not enrolled, which would decrease the generalizability of this large important trial. Rich et al. (Pediatrics 2010, 126: e215-e221) found that infants who were approached for participation in SUPPORT were significantly different from non-approached infants who were eligible for this trial and were born in the recruiting centers. Enrolled infants were more likely to be white, have mothers with better education and health insurance, and have prenatal care. They were less likely to be in the most immature gestational age week for this study. Antenatal Consent has been shown to limit the enrollment of the sickest infants in studies by eliminating the ability to obtain consent from

mothers with limited prenatal care and/or emergent deliveries. We believe that the use of antenatal consent would adversely affect the generalizability of the data obtained. A member of the research team will approach the parents after delivery to discuss the study. A delayed informed consent will be obtained to use the infant's data in the study and obtain neurodevelopmental follow up data.

Therefore pregnant women at <32 weeks gestation dated by their earliest ultrasound or last menstrual period will be approached for consent. In the past 12 months, the Sharp Mary Birch obstetric service had 150 premature newborns delivered by C/S. The demographics of our population are about 40 percent Caucasian, 30 percent Hispanic, 15 percent Asian Pacific

Islander, 7 percent African American and 8 percent other (Native American, etc.).

Inclusion and exclusion criteria are shown in **Table 1.**

| **Table 1** | **INCLUSION**  **Criteria** | **EXCLUSION**  **Criteria** | **REASON** |

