| --- | --- | --- | --- |
| Gestational Age | 23 to 31+6 weeks |  | This GA most likely to require resuscitation interventions. Delayed consent will be obtained to allow for urgent unplanned deliveries to be included in the trial such as emergency C-Section, etc. |
| Parental refusal to participate |  | X | Parents may refuse participation antenatally or after delivery. |
| Congenital Anomalies |  | X | Increased risk for poor long-term outcomes and death. |
| Moderate to severe head bruising upon delivery |  | X | Difficulty in assessing skin integrity with dark bruising |

***Study Protocol:*** Currently, all infants taken to the resuscitation suite have recordings of heart rate, oxygenation, and airway pressure, along with simultaneous video recording. These recordings are reviewed monthly as part of our quality improvement process. Routine use of EEG or NIRS monitoring may be used per physician preference. Therefore the only additional component of the study will be the placement of electrodes (EEG) and a single sensor (NIRS) at the time of birth. ECG will be available in half of the infants per randomization during resuscitation. Upon identification of an eligible delivery, an additional research coordinator will be on standby to assist with placement of sensors.

EEG electrodes, NIRS probes, ECG electrodes and pulse oximetry will be applied within 60 seconds of the newborn being placed on the warmer. We piloted this procedure in four recent emergency C/S deliveries in which the research team successfully applied adhesive sensors within 60 seconds without interfering with resuscitation. The average time to display EEG and NIRS signals were 32 and 63 seconds, respectively. The placement of the sensors and tracing from one example are shown in **Figure 3**. (*Note – Removed for inclusion of protocol in publication*) While saturation and heart rate data will be available to the clinical team, data from both aEEG and NIRS will be blinded.

Additional monitoring will begin once the newborn is in the NICU. Electrical Cardiometry sensors (which can measure cardiac output and stroke volume) using four EC sensors (Electrical Cardiometry, Cardiotronic, La Jolla, CA) will be placed on the newborn’s chest.

Cerebral StO2, cardiac output, and stroke volume will be recorded every two seconds and linked with other variables that will be downloaded from the infant’s hospital bedside monitor.

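### A section heading announces stratification but the protocol names no factor; gestational age, known before birth, is used neither in the allocation rule nor in the stated two-by-two test of the ECG comparison

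*Protocol*

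**What the plan says.** - **Allocation.** The proposal narrative (Goals, hypothesis and objectives) will "make ECG available in half of the infants (by randomization at the time of delivery by the research team, in opaque sealed envelopes" and then "record the amount of resuscitation needed". The Study Protocol text adds "ECG will be available in half of the infants per randomization during resuscitation". Neither place mentions strata, blocks or the number of envelope series.
- **Heading.** Under Recruitment and Retention of Subjects, the first paragraph is headed "Recruitment/Consent/Stratification". The text below it covers the parent advisory group, delayed consent, dating of the pregnancy, demographics and eligibility. It names no stratification factor, and nor does the rest of the protocol.
- **Range.** Table 1 admits infants of "23 to 31+6 weeks" and gives as its reason "This GA most likely to require resuscitation interventions". Pregnancies are dated by earliest ultrasound or last menstrual period, so gestational age is available when the envelope is opened. It is also on the list of data collected for every infant.
- **Analysis.** The Statistical Analysis paragraph gives a 2 x 2 chi-square at each minute, with phi, relative risk and odds ratio, for a primary efficacy endpoint that it does not name. It also lists linear, logistic and generalized linear models, without saying that gestational age enters the ECG comparison.
- **Size.** "Number of subjects to be studied: 130".

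**The concern.** A heading that promises stratification over text that supplies none leaves the people preparing the envelopes unable to tell which design was meant. A later analysis plan cannot fully repair this, because the envelopes exist before the first delivery and an allocation already made cannot be stratified afterwards.

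Gestational age is the natural candidate. The eligible range spans nine weeks of gestation, the randomised question is how much resuscitation infants need, and the variable is known at allocation. Leaving it out of both the allocation and the stated test has two costs. In this one trial the arms may differ by chance in how many very immature infants they hold, which makes a crude result harder to interpret. The comparison also forgoes precision in a trial of only 130 infants.

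**Working it through.** The protocol states no imbalance probability and no gestational-age distribution, so there is no figure to reproduce.

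**Inputs.** From the protocol: 130 infants, half with ECG, hence 65 per arm. Assumed: the most immature infants make up a share p of the cohort, varied from 10% to 50%. A cut at 28 weeks with p = 30-40% is one illustration. The calculation also assumes allocation without strata.

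**Chance of imbalance.** Let K of the 130 infants be most immature and x of them receive ECG. Then x is hypergeometric and the difference between arms is d = (2x - K)/65, with SD(d) = (2/65) × √(65 × p(1-p) × 65/129).

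- K = 39 (30%): √(65 × 0.30 × 0.70 × 65/129) = 2.62, so the SD is 2 × 2.62/65 = 8.1 points.
- K = 52 (40%): √(65 × 0.40 × 0.60 × 65/129) = 2.80, so the SD is 8.6 points.

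Ten points is 6.5 infants out of 65. So |2x - K| must reach 7 if K is odd and 8 if K is even, which makes the exact values uneven. The normal approximation, 2 × [1 - Φ(0.10/√(p(1-p) × 2/65))], smooths this out.

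| Share | K | Exact chance of 10 points or more | Normal approximation |
|---|---|---|---|
| 10% | 13 | 7.6% | 5.7% |
| 15% | 20 | 8.7% | 11.0% |
| 20% | 26 | 12.4% | 15.4% |
| 25% | 32 | 15.3% | 18.8% |
| 30% | 39 | 25.1% | 21.3% |
| 33% | 43 | 26.3% | 22.6% |
| 40% | 52 | 21.0% | 24.5% |
| 50% | 65 | 29.3% | 25.4% |

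At these shares the exact range is about 8-29% and the smoothed range about 6-25%. For p = 30-40% the smoothed value is 21-24.5%. Exact values for the whole counts from 39 to 52 alternate around it, between about 18% and 28%. The exact chance of 15 points or more is 5.5% at K = 39 and 10.7% at K = 52. All of these count either direction; a given direction has half the chance.

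**What an imbalance does.** Assume an intervention is needed by 60% of the most immature infants and 20% of the others, with p = 35%.

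- Shift from a 10-point imbalance: 0.10 × (0.60 - 0.20) = 4 points.
- Overall risk: 0.35 × 0.60 + 0.65 × 0.20 = 0.34.
- Unadjusted standard error: √(2 × 0.34 × 0.66/65) = 8.3 points. The shift is 4/8.3, or about half a standard error.
- Mean within-stratum variance: 0.35 × 0.24 + 0.65 × 0.16 = 0.188.
- Standard error with gestational age removed: √(2 × 0.188/65) = 7.6 points.
- Variance ratio: (0.34 × 0.66)/0.188 = 1.19. The precision gained is what about 19% more infants would give.

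**After stratifying.** With two strata and permuted blocks of 4 (block size assumed for the calculation), simulation for K from 26 to 52 gave no difference of 10 points. The largest was about 2.5 points, before any loss from refusals.

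**The case against.** The strongest reply is that unstratified randomisation of 130 infants at one centre is legitimate, and that the ECG question is an addition to a mainly observational study. Three stronger readings are tempting, and the protocol supports none of them.

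- **That nothing is stratified and all infants come from a single envelope series.** The protocol is silent on series, strata and blocks. The heading, if anything, hints at an intention whose detail was left out. What can be said is that no factor is specified.
- **That a 20-25% chance of imbalance is a property of this trial.** It depends on an assumed share of 30-40%. A narrow definition of most immature, such as 10% of infants, brings it to about 6-8%.
- **That imbalance biases the ECG result or invalidates the test.** Under randomisation the chi-square keeps its nominal error rate, because its sampling error already includes chance imbalance. The 4-point shift is half a standard error and rests on assumed risks.

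Two further points stand in part. Table 1 explains why the whole range is eligible; it does not describe a gradient within it, so the link between gestational age and resuscitation is plausible rather than documented. Covariates may be set in an analysis plan that is not shown, and the protocol does not say that its chi-square is the ECG comparison. That weakens the analysis half of the point. It does not touch the allocation half, which has to be settled before the first envelope is opened.

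**Conclusion.** The point holds as a cheap improvement, not as a defect of validity. The textual gap is certain: stratification is announced and no factor is given. The statistical cost is modest. The chance of a 10-point or larger imbalance is about 8-29% for shares of 10-50%, and the standard error is about 8.3 rather than 7.6 points. The first figure rests on 65 per arm, allocation without strata and an unstated share. The second rests on assumed risks of 60% and 20% with a share of 35%.

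**What to change.** Preferred: state that randomisation is stratified by gestational age (for example below 28 weeks, and 28 weeks or above), with a separate envelope series for each stratum in permuted blocks of varying size. Include gestational age in the ECG comparison.

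Alternative, if allocation will not be stratified: delete the word from the heading and prespecify gestational age as a covariate in the ECG comparison.

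The cost is a sentence or two in the allocation and analysis text and, for the first option, a second envelope series. Staff must pick the right series at urgent deliveries, though gestational age is already being checked there for eligibility. Balance among analysed infants may be slightly worse than at allocation. Consent follows delivery, parents may refuse then, and the protocol allows for 20% refusal, even though it also says "We do not anticipate that any subjects would drop out since the intervention is performed at birth". Adjusting for gestational age deals with what imbalance remains.

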# Methods used to achieve our goals.

[figure not shown]
We previously demonstrated the feasibility of measuring the physiological changes of premature newborns in the delivery room (**Figure 1**). [16, 17] We routinely monitor heart rate, oxygen levels, and the amount of breathing assistance given to all of our premature babies.

[figure not shown]

**Figure 1**

We will combine the ability to monitor brain activity using aEEG, and brain perfusion with near-infrared spectroscopy (NIRS) to capture the brain’s oxygen usage at birth. Both EEG and NIRS are acquired using inexpensive,

widely available, FDA-approved adhesive electrodes. Our last few trials have been focused on early interventions on preterm infants while monitoring the infants’ immediate

response by changes in vital signs. [11, 18, 19] These trials have provided us experience in monitoring infants *immediately upon delivery.*

Additionally, all enrolled newborns will receive a detailed brain ultrasound within 24 hours of birth and again at one week. If clinically indicated, a magnetic resonance imaging (MRI) will be performed when full-term equivalence is reached. The brain ultrasounds will alert us to any bleeding in the brain, and the MRI will reveal the full extent of any brain injury due to prematurity.

Non-invasive neural monitoring by NIRS and amplitude integrated EEG (aEEG) are able to detect differences in early brain injury.

How does NIRS work? NIRS is a technology that allows non-invasive continuous real-

time measurement of the regional tissue perfusion of organs such as the brain. Hemoglobin, which carries oxygen in the bloodstream, absorbs near-infrared light differently depending on whether the hemoglobin is carrying oxygen or not. NIRS measures the absorption of near- infrared light by the brain to measure how well the brain is using oxygen. Low brain perfusion (cerebral StO2) as measured by NIRS within the first few days of life has been shown to be associated with adverse neurological outcome and brain bleeding. [20, 21] In a single observational study, infants who had very

low cerebral StO2 in the delivery room (<10th

[figure not shown]

**Figure 2. Delivery room NIRS of 2 preterms that developed brain bleeds (IVH)**

percentile of normative range) were shown to have an increased risk of developing brain bleeding (**Figure 2**). [9]

How does EEG work? EEG directly

measures brain activity similar to how an

ECG measures heart activity. Recent studies

have provided data about how preterm electrical

brain activity is an indicator of brain injury. [22, 23] We will combine aEEG with NIRS to enrich

the information we obtain about the preterm brain during birth resuscitation. The interplay of

brain oxygenation and electrical brain activity has been demonstrated in a single study by a positive correlation between cerebral StO2 and aEEG in the delivery room. [24] We have started testing the application of EEG sensors in the delivery room using a simple 4-lead montage that can be applied to the forehead. [24]

Our Research Team

[name] (PI) has successfully conducted several randomized controlled trials in resuscitation and placental transfusion. [10, 11, 18, 25] He has performed studies demonstrating the benefits of UCM in premature infants, studied blood flow during caffeine and surfactant administration, and the use of continuous cardiac monitoring by electrocardiogram (ECG) in the delivery room and by Electrical Cardiometry (EC) in the intensive care unit. He successfully developed an effective collaboration with the Division of Perinatology with his previous trials. [10, 11] [name] has led and designed a number of clinical trials both single site and multicenter and is considered one of the world’s experts in neonatal resuscitation. [name] is a Gerber Foundation funded neonatal neurologist who has focused on protecting the newborn brain and is currently studying the effects of resuscitation on early EEG and NIRS.

The Neonatal Research Institute Coordinators and Research Assistants, have extensive experience in multicenter as well as single center studies. They will coordinate the trial, assist in obtaining informed consents, and ensure data collection and clinical specimens are obtained in a timely fashion in keeping with accepted research standards to ensure all aspects of the protocol are followed.

# Size of the population to be studied in terms of age, gender, ethnicity, the source of subjects and the recruitment process.

In 2014 more than 9,400 babies were born at Sharp Mary Birch Hospital for Women and Newborns, and 1,500 babies were admitted into the NICU. In our most recently completed trial in premature infants with identical eligibility criteria (23-32 weeks gestation), we recruited 150 subjects in less than 2 years. (Platform Presentation: Katheria et al, E-PAS 2015). Therefore, we are confident that we will be able to enroll the 130 newborns needed over the two year grant period. This figure is also conservative to include a parental refusal rate of 20 percent since we do not anticipate many parents would refuse to participate given the minimal risks of the study. Every premature newborn from 23 to 32 weeks gestation born at Sharp Mary Birch will be considered for enrollment until we reach our target of 130 newborns over the two year period.

**Study Timeline:** We anticipate it will take 18 months to recruit 130 infants and six months to

collect and analyze data for publication and presentation at a national meeting (total 24 months). We do not anticipate that any subjects would drop out since the intervention is performed at birth.

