# Description of evaluation measures to assess project results and outcomes.

Our overall aim for this project is to provide preliminary data about the premature brain during the birth transition and resuscitation. Increased understanding of how the premature brain responds during this critical time will provide a physiological basis of improving the resuscitation process, will demonstrate the feasibility of such monitoring, and will be used to determine optimal practice for these vulnerable infants and improve their quality of life. After the successful conclusion of this project, we will apply specific interventions at birth in the preterm population and evaluate the resultant effects on neuro-monitoring. This will be in the context of a large randomized controlled trial powered to demonstrate improvements in long-term neurodevelopmental outcomes in children.

Given the known association between extensive resuscitation and outcomes such as bleeding in the brain and death, we expect to find physiological changes in newborns

immediately after birth and during the first 72 hours of life. We expect to find very early, potentially correctable changes in physiology that may be able to protect the brain before injury can take place.

We will also collect routine follow-up visit information at 18–30 months corrected gestational age to see if there is any correlation between NIRS and aEEG during the first 3 days of life to long term neurodevelopmental outcomes.

**STATISTICAL CONSIDERATIONS (Sample Size and Power Calculation):** All aspects of data

analysis and statistical investigations will be directed by [name], who has formal training in Statistics and has expertise in multivariate datasets such as these.

**Statistical Analysis**: To test the primary efficacy endpoint a 2 x 2 chi-square test will be

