conducted at each one minute interval, and the attendant effect size for the 2 x 2 contingency analyses (i.e., phi) will be reported. As well, relative risk (RR) and odds ratio (OR) statistics will be reported (along with 95 percent confidence intervals). For interval-level, continuous outcomes one-way ANOVA will be conducted and all assumptions will be tested/examined (normality, homogeneity of variance, etc.). Nonparametric options (e.g., Mann-Whitney) will be considered in case remedial measures such as transformations do not meet the parametric assumptions. We will compare continuous data measures averaged over each MOL using multi- variate linear regression analysis. We will use linear, logistic or generalized linear models to evaluate demographic variables and clinical outcome variables all using SPSS vs. 22.0 or Stata 11.0.

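### Multiples are not excluded, yet the named tests treat all infants as independent, so intervals and p-values may be modestly miscalibrated, mainly for the StO2/aEEG associations

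*Protocol*

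**What the plan says.** **Who enters.** The Protocol's opening page gives "Number of subjects to be studied: 130", and the section on the size of the population says "Every premature newborn from 23 to 32 weeks gestation born at Sharp Mary Birch will be considered for enrollment". The exclusions in Table 1 are parental refusal, congenital anomalies and "Moderate to severe head bruising upon delivery". Multiple birth is not listed, and there is no limit of one infant per mother. Twins or siblings are not mentioned anywhere in the document.

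**How ECG is allocated.** ECG is to be available in half of the infants, by "randomization at the time of delivery by the research team, in opaque sealed envelopes". No rule says whether siblings are randomised individually or together.

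**How the data are analysed.** The Statistical Analysis paragraph reads "To test the primary efficacy endpoint a 2 x 2 chi-square test will be" and continues "conducted at each one minute interval, and the attendant effect size for the 2 x 2 contingency analyses", with risk ratios, odds ratios and 95% confidence intervals. It then says "For interval-level, continuous outcomes one-way ANOVA will be conducted", with Mann-Whitney as a fallback. Linear, logistic and generalized linear models are also named. No method for correlated infants appears.

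**What is recorded.** Table 2 has 13 maternal items and 6 infant clinical items, followed by the endpoints. Plurality is not among them. Mothers are themselves enrolled, and data come from both mothers and newborns.

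**The concern.** Siblings share gestational age, much of their antenatal exposure (steroids, magnesium, chorioamnionitis) and often the mode of delivery. Their outcomes are therefore likely to be correlated. A chi-square test, a one-way ANOVA and an ordinary regression all count two siblings as two independent pieces of information.

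What this does depends on how the explanatory variable behaves within a pair. If siblings tend to have the same value, the naive standard error is too small. If they tend to have opposite values, it is too large. If the values are unrelated, it is about right.

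This matters most for the primary hypothesis, that low brain perfusion and low brain activity at birth go with brain bleeding and death. That hypothesis is observational, so no allocation scheme breaks the link between siblings' exposures. In the ECG comparison, the direction of any error depends on the sibling rule that the Protocol leaves unstated.

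**Working it through.** **Inputs from the Protocol:** N = 130 infants; ECG in half of them; tests and intervals that assume independence. No significance level, power, event rate or effect size accompanies the 130, so it cannot be reproduced. It is used here only as N.

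**Assumptions (the Protocol gives no figures):** share of infants in twin pairs s = 0.2 to 0.3; within-pair outcome correlation ρy = 0.3 to 0.6; within-pair exposure correlation ρx as set out below; two-sided nominal 5%. Higher-order multiples are ignored.

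**Formulas.** With pairs as the only clusters:

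- design effect DE ≈ 1 + s × ρx × ρy
- effective N = 130 / DE
- true level of the naive test = 2[1 − Φ(1.96/√DE)]

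The possible cases differ only in ρx.

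| Case | ρx | DE | Effective N | True level |
|---|---|---|---|---|
| StO2/aEEG associations | 0.3 to 0.6 | 1 + 0.2×0.3×0.3 = 1.018 to 1 + 0.3×0.6×0.6 = 1.108 | 128 to 117 | 5.2% to 6.3% |
| Siblings always share exposure or arm | 1 | 1 + 0.2×0.3 = 1.06 to 1 + 0.3×0.6 = 1.18 | 123 to 110 | 5.7% to 7.1% |
| ECG, siblings randomised independently | 0 on average | 1 | 130 | 5% |
| ECG, siblings always split | −1 | 1 − 0.06 = 0.94 to 1 − 0.18 = 0.82 | – | 4.3% to 3.0% |

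**Interval width.** The correct standard error is √DE times the naive one. In the first case that is √1.018 = 1.009 to √1.108 = 1.053, or intervals about 1% to 5% wider. In the second it is √1.06 = 1.030 to √1.18 = 1.086, or 3% to 9% wider.

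**Check by simulation.** The naive 2 x 2 chi-square was simulated with N = 130, an assumed event rate of 0.30 and 40,000 runs per scenario. At s = 0.3 and ρy = 0.5:

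- siblings in the same arm: 6.7% (formula 6.8%)
- siblings split: 3.3% (formula 3.4%)
- siblings randomised independently: 4.9%

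Across s = 0.2 to 0.4 and ρy = 0.3 to 0.8, independent randomisation gave 4.9% to 5.1%.

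**Wider assumptions.** With s from 0.1 to 0.4 and ρy from 0.1 to 0.8, the level runs from 5.1% to 8.8% if siblings always share a group, and from 4.9% down to 1.8% if they are always split.

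**The case against.** A reader might infer that the trial's intervals and p-values are simply wrong, and that the listed data rule out later correction. The documents support neither.

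- **Size is assumed.** Eligibility of multiples follows from broad enrolment wording and the absence of an exclusion. Neither their number nor any correlation is stated, and over plausible inputs the error is modest.
- **The ECG comparison may be unaffected.** ECG in half of the infants reads most naturally as per-infant randomisation, under which the naive test averages close to 5%. The chi-square is tied to an efficacy endpoint, which probably means this comparison. The fixed primary test may then be the one least affected.
- **The full pair design effect overstates the associations.** StO2 and aEEG are measured in each infant and can differ within a pair, so 1.06-1.18 is an upper case.
- **A sibling link is probably recoverable.** Table 2 lists no subject identifiers of any kind, so a missing mother ID there is not evidence that none exists. Relating maternal variables to infant outcomes already requires a mother-infant link.
- **Some of this is commonly left to an analysis plan.** A plan that is not shown could specify clustering, the Protocol says ANOVA assumptions will be examined, and the project aims at preliminary data.

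These points limit size and certainty. They do not remove the problem: the Protocol itself names tests that ignore sibling correlation, and the sibling randomisation rule belongs in the Protocol, since staff need it at delivery.

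**Conclusion.** The point holds in a limited form. Multiples can enter, and the analysis as written ignores their correlation.

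For the observational associations the likely error is towards intervals that are too narrow. Under the stated assumptions a nominal 5% test runs at about 5.2% to 6.3%; 5.7% to 7.1% requires siblings always to share exposure or arm.

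For the ECG comparison the direction is open: near 5% on average with independent randomisation, anti-conservative if siblings share an arm, conservative if they are always split. All sizes rest on an assumed twin share and assumed correlations. The documents do not show that any particular result would change. The correction is still worth making because it is cheap and the allocation rule must be settled before enrolment.

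**What to change.** 1. For the primary and continuous comparisons, fit the generalized linear models already named under Statistical Analysis by GEE, or with cluster-robust standard errors, with the mother as the cluster. Suitable links still yield the risk ratios and odds ratios with 95% intervals. Under the assumed twin share there would be about 110 to 117 mothers (130 × 0.7 + 130 × 0.3/2 = 110.5; 130 × 0.8 + 130 × 0.2/2 = 117), so there is no shortage of clusters.
2. Carry plurality and a mother ID in the analysis data set.
3. State whether siblings are randomised individually or together, and use the same clustered model in either case.

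The cost is two data fields, a few sentences of text and slightly wider intervals. No additional infants are needed to make the change.
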